#### Assessments

Independent assessments are being made of index and control participants by the two trained data collectors. These assessments are made in the Children’s Centres for the first two assessments (and occasionally in families’ homes) and the final assessment is made at the School of Psychology and Clinical Language Sciences of the University of Reading.

The assessments being made are as follows:Child outcomes

*Cognitive development (primary outcome)*

*Language*: expressive language is being assessed using the Early Years Toolbox (EYT) [20], administered using iPad technology, and receptive language using the Clinical Evaluation of Language Fundamentals (CELF-2) [25]. A parental report measure of language is also being administered, the Communication Development Inventory (CDI) [26].

*Attention*: this is assessed by deriving an index from the Go-No-Go sub-test of the EYT, by the Early Child Vigilance Task (ECVT) [27], and by observing behaviour in “the three toys” task [13, 28], and by parent report on the Strengths and Difficulties Scale (SDQ) [29] and the Child Self-Regulation and Behaviour Questionnaire (CSBQ) of the EYT [20].

*Executive function*: this is being assessed using the EYT, Block design (WPPSI-IV) [30], Digit span [31], the Following Instructions task [32], and persistence and strategies in the Frustration task of the Laboratory Temperament Assessment Battery (Lab-TAB) [33], and by parent report on the CSBQ [20].
*Child social development (secondary outcome)*

*Theory of mind and emotional understanding*: this is being assessed using a battery of tasks based on Wellman and Liu [34], Hughes et al. [35] and Denham [36]. These tasks comprise brief, typically puppet-enacted scenarios, during which young children are asked to judge the different perspectives, knowledge, desires and emotions of the characters.

*Empathy*: a “help task” paradigm is being administered in which a researcher feigns experiencing a problem (i.e., being unable to find something that is in view of the child) and the child’s response is observed [15, 37, 38].

*Altruism*: a modified version of an altruism task [39] is being used.

*Prosocial behaviour*: this is being measured by parent report using the SDQ [29].
*Child behaviour problems (secondary outcome)*

These are being assessed by maternal report and direct observation. For maternal report we are using the SDQ [29]. Child behaviour is also assessed by direct observation during the parent-child interactions in the “don't touch”’ task (in which the child is prohibited from touching attractive toys) [40–42]. 
*Emotion regulation (secondary outcome)*

This is being assessed by direct observation using the Distress-Anger/Frustration component of the Lab-TAB for pre-school children, and by parent report on the CSBQ [20].Parenting (secondary outcome)

*Sensitivity and reciprocity* [13, 15] and *cognitive scaffolding* are being assessed by direct observation of parent-child interaction in book-sharing and a problem solving task. *Mental state talk* is also assessed during book-sharing.

*Parent behaviour management strategies*: these are being assessed by maternal report and direct observation. Parents complete the Child Rearing Discipline Scale [43], and they are directly observed during the “do not touch” task described above [39, 43].

### Potential moderators

The following variables will be used as potential moderators: family socio-economic status, parental education, monolingualism status, ethnic group, parental mental health (HADS; [44]), stress (PSI [45]), and baseline book-sharing, child sex, age and birth order.

### Data management

Data are submitted to a secure University server. Participants are allocated personal identification numbers that are used in all study records to protect their identity and maintain confidentiality. All child assessments and caregiver-child interaction tasks are video-recorded, for both coding and quality control purposes. Videos are labelled by the assessors and saved on the secure server at the end of each day.

### Data analysis

Data analysis will be completed by a designated statistician independent from study investigators. Group baseline differences will be assessed using the independent samples *t* test, Mann-Whitney U test, and chi-squared test. Analysis of baseline group differences will include socio-demographic data, such as child sex, and household factors (e.g., income, relationship status). The primary and secondary outcomes will be analysed using linear mixed models which can account for clustering of individuals within the Children’s Centre and for repeated assessments within individuals (for outcomes measured at multiple time points). Intervention effects will be assessed post intervention and at follow-up, and will be adjusted for the child’s age, sex and baseline scores (where applicable). Further socio-demographic factors may also be investigated as covariates. If the necessary assumptions of the models do not hold, suitable alternative models will be fitted. Intention-to-treat analysis will be used to examine intervention effects [45]. The amount and pattern of missing data will be examined and will be addressed using multiple imputation where appropriate.

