## Methods

### Study design

The study is a cluster RCT. Reading has 13 Children’s Centres, but one is an outlier in terms of the socio-demographic profile of both ward and attenders. The remaining 12 Centres have been randomly assigned to the index condition (6 Centres), which is receiving training in dialogic book-sharing, and a control condition (6 Centres) receiving the normal input from the Children’s Centres. Data are being collected at baseline, post-intervention, and at 4–6 month follow up.

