### Eligibility criteria

#### Sample

The sample comprises carers (mainly mothers) of children attending the Reading Children Centres, whose children are aged 28–45 months at recruitment and where English is spoken at home. There are 3074 children under 5 years of age living in Reading within the 20% most deprived local super output areas (LSOAs) [22], representing 25% of all Reading children of this age. The 12 participating Children’s Centres in Reading are situated in these areas. They target the most vulnerable families in these most deprived communities, and attendance from this group is consistently over 70% at all Children’s Centres, with these attendees representing the vast majority of Children’s Centre clientele, ensuring socio-demographic homogeneity of the appropriate target population across centres (intra-cluster correlation estimate = 0.04).

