The primary outcome in the EPICC trial is child cognition (i.e., language, attention and executive function). Since only one study has examined the impact of book-sharing training on executive function [20], and only one trial has reported an outcome for attention [14], we must calculate sample size from the language variable. The most recent meta-analysis [23] included the 10 RCTs of book-sharing interventions that targeted parents of pre-school children and reported the outcome of child expressive language. Although all but one of these studies showed positive benefit to the children’s language (the exception was one that comprised just three 5-min sessions [24]), there was considerable variability in the nature and duration of the intervention programmes, and there was significant variability in terms of child outcome [23]. The overall effect size for expressive language in the 10 studies was 0.57. However, it is too conservative to base the sample size for the current trial on the effect size for all 10 studies, as the average effect size was 0.88 for the three trials that used a group format of dialogic reading instruction of the form to be used in the current study, and the lowest effect size (0.04) was reported in a study involving just 5-min training sessions [24]. A mid-range medium effect size is therefore justified by the previous data. Using the statistical package R, with *d* = 0.66, within the cluster design, an index and control sample of 96 carers in each are required (with alpha = 0.05 and beta = 0.90). With an addition of 10% to account for sample loss, a total sample of 214 carers is required - i.e., two groups of 107.

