### Outcomes

For details of outcomes see Table 2

**Table 2 Tab2:** Study outcomes and measures

				Post allocation	
			Week 1–4	Week 18–22	Week 30–38
Outcomes	Concept	Measures	Baseline	Post	Follow up
Child cognitive development (primary outcome)	Language				
	Expressive	EYT (expressive vocabulary)	X	X	X
		Parent report: CDI	X	X	X
	Receptive	Pre-school CELF-2			X
		Parent report: CDI	X	X	X
	Attention				
		EYT (Go No Go)	X	X	X
		ECVT	X	X	X
		Observation: 3 toys task	X	X	X
		Parent report: SDQ and CSBQ	X	X	X
	Executive function				
	Non-verbal reasoning	WPPSI block design		X	X
	Task shifting	EYT (card sort)			X
	Phonological working memory	Digit span		X	X
		Following instructions		X	X
	Persistence and strategies	Observation: Lab-TAB	X		X
	Inhibition	EYT (Go No Go)	X	X	X
	Self- regulation	Parent report: CSBQ	X	X	X
Child social development (secondary outcome)	Theory of mind and emotional understanding	Observation: ToM package	X	X	X
	Empathy	Observation: help task	X	X	X
	Altruism	Observation: token sharing			X
	Pro-social behaviour	Parent report: SDQ	X	X	X
Child behavioural problems (secondary outcome)		Observation: don't touch task	X	X	X
		Parental report: SDQ	X	X	X
Child emotion regulation (secondary outcome)		Observation: Lab-TAB	X		X
		Parent report: CSBQ	X	X	X
Parental sensitivity and reciprocity (secondary outcome)		Observation: book-sharing	X	X	
Parental cognitive scaffolding (secondary outcome)		Observation: book-sharing and puzzle task	X	X	
Parental mental state talk (secondary outcome)		Book-sharing	X	X	
Parental behavioural management strategies		Observation: don't touch task	X	X	X
		Parent report: Discipline Scale	X	X	X
Parental stress and mood		Parent report: PSI	X	X	X
		Parent report: HADS	X	X	X

*Abbreviations: EYT* Early Years Toolbox, *CDI* Communication Development Inventory, *CEL*F Clinical Evaluation of Language Fundamentals, *ECVT* Early Child Vigilance Task, *SDQ* Strengths and Difficulties Questionnaire, *WPPSI* Wechsler Preschool and Primary Scale of Intelligence, *Lab-TAB* Laboratory Temperament Assessment Battery, *CSBQ* Child Self-Regulation and Behaviour Questionnaire, *PSI* Parenting Stress Index, *HADS* Hospital Anxiety and Depression Scale

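### Five primary cognitive measures without a baseline would be adjusted for age and sex but for no baseline cognitive score, although related tests are collected at baseline

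*Protocol article*

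**What the plan says.** The Data analysis section of the protocol article specifies linear mixed models for the primary and secondary outcomes, with effects adjusted for the child's "age, sex and baseline scores (where applicable"). It adds that further socio-demographic factors may be looked at as covariates. It names no substitute for an outcome that has no baseline of its own, and it does not forbid one.

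Table 2, in the Outcomes section, gives the assessment times under child cognitive development, the primary outcome:

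- Follow-up only: "Pre-school CELF-2" and EYT card sort.
- Post-intervention and follow-up only: "WPPSI block design", digit span and "Following instructions".
- Measured at baseline: EYT expressive vocabulary, CDI, EYT Go/No-Go, ECVT, the three toys task, SDQ and CSBQ parent report, and Lab-TAB.

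CELF-2 is the only direct test of receptive language. The other four measures without a baseline are four of the six direct executive-function tests; only Go/No-Go and Lab-TAB in that group have one.

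**The concern.** A covariate rule tied to each outcome's own baseline leaves these five measures without any measure of the child's starting ability. Age and sex remain in the model, but they cannot remove a difference in ability between children of the same age and sex.

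This matters more than usual because few units are randomised. The Study design section says "The remaining 12 Centres have been randomly assigned to the index condition (6 Centres"), with six control Centres. The Randomisation section describes minimisation on ward-level deprivation and ethnic profile. That helps with social composition but does not balance child cognition directly. A chance difference in starting ability between the arms would carry through to the estimated effect on these five measures, and variance that an existing baseline test could explain would stay in the standard error.

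**Working it through.** **Inputs from the protocol article**

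- Sample section: "with alpha = 0.05 and beta = 0.90", read here as two-sided alpha 0.05 and power 0.90; *d* = "0.66, within the cluster design"; "intra-cluster correlation estimate = 0.04"; 96 carers per arm; 10% loss; 214 in total.
- Study design section: 6 Centres per arm. Equal Centre sizes are assumed, so m = 96/6 = 16 per Centre.

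**Assumption.** The documents give no correlation between a baseline test and the five outcomes. A partial correlation r, given age and sex, of 0.3 to 0.6 is used.

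**Step 1: reproduce the stated sample size, with no baseline covariate.**
Variance of the difference in SD units = (2/6) × [ICC + (1 − ICC)/m] = (1/3) × (0.04 + 0.96/16) = (1/3) × 0.10 = 0.0333, so SE = 0.183.
With a t test on 2 × (6 − 1) = 10 degrees of freedom and non-centrality 0.66/0.183 = 3.61, power is 0.902. Solving for 90% power gives m = 15.84, rounded up to 16, which is 96 per arm. Then 96/0.9 = 106.7, rounded up to 107 per arm, or 214 in total. The plan's figures reproduce, and no baseline adjustment enters them.

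**Step 2: add a baseline score.**

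- Both levels: variance = (1/3) × (1 − r²) × 0.10.
- Individual level only: variance = (1/3) × [0.04 + 0.06 × (1 − r²)].

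| r (assumed) | SE, both levels | SE reduction | SE, individual only | SE reduction |
|---|---|---|---|---|
| none | 0.183 | – | 0.183 | – |
| 0.3 | 0.174 | 4.6% | 0.178 | 2.7% |
| 0.4 | 0.167 | 8.3% | 0.174 | 4.9% |
| 0.5 | 0.158 | 13.4% | 0.168 | 7.8% |
| 0.6 | 0.146 | 20.0% | 0.162 | 11.5% |

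**Step 3: what this means for power.** Over r = 0.3 to 0.6, the effect detectable with 90% power falls from 0.66 to between 0.63 and 0.53 (both levels), or to between 0.64 and 0.58 (individual level only). At *d* = 0.57, the ten-trial average quoted in the Sample section, power rises from 0.80 to between 0.84 and 0.94 (both levels), or to between 0.82 and 0.89 (individual level only).

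**Step 4: chance imbalance.** A baseline score with the same ICC of 0.04 has a between-arm difference with SE 0.183 SD, so a 95% range of ±1.96 × 0.183 = ±0.36 SD. Left unadjusted, a difference at the edge of that range moves the outcome contrast by r × 0.36: about 0.11 SD for r = 0.3 and 0.21 SD for r = 0.6. Set against *d* = 0.66, that is roughly one sixth to one third.

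**The case against.** The strongest reply is that this is detail for the analysis plan. The article states the covariate set at ordinary protocol depth, its wording does not limit baseline scores to the same instrument, and an analysis plan not shown here could name substitutes. That lowers the certainty about what will be done. It does not remove the point: the article does state a covariate rule, its natural reading gives these five measures no baseline score, and the only extension offered is socio-demographic and optional. If the rule is meant to allow a substitute, the choice is left open for measures of the primary outcome.

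A second reply concerns size, and it stands. Age over 28 to 45 months may already absorb part of what a baseline test would explain, so raw correlations overstate the gain. As an illustration, suppose age correlates 0.4 with both tests. A raw correlation of 0.4, 0.5 or 0.6 then becomes a partial one of (r − 0.16)/0.84 = 0.29, 0.40 or 0.52, and the SE reduction, if it acts at both levels, is about 4%, 9% or 15%. This is why r above is defined as partial, and why the individual-level case is shown.

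A reader might also infer that these five measures get no baseline adjustment of any kind, that their effect estimates would be biased, or that the trial is underpowered for them. The documents support none of these. Age and sex are in every model. Under randomisation an analysis without a proxy remains valid, and chance imbalance is already part of its standard error. The stated power never relied on baseline adjustment.

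**Conclusion.** The point holds as a loss of efficiency that can be avoided at almost no cost. Five primary cognitive measures would, as the rule reads, be analysed with age and sex but without a baseline cognitive score, while related tests are collected at baseline in the same children. For an assumed partial correlation of 0.3 to 0.6, the forgone reduction in standard error is about 5% to 20% if the substitute works at both levels, or about 3% to 11.5% if only at the individual level. These ranges rest on ICC 0.04, 16 children per Centre and a correlation that the documents do not supply.

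It would be tempting to apply the same rule to altruism, a secondary measure taken only at follow-up. Nothing in the documents makes vocabulary or inhibition an evident substitute baseline for altruism, so the point is confined to the five cognitive measures.

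**What to change.** In the Data analysis section, replace the open qualifier on baseline scores with a fixed rule: each outcome is adjusted for its own baseline where that was measured, and otherwise for a named child-level baseline score chosen before analysis. For example:

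- CELF-2: baseline EYT expressive vocabulary, or baseline CDI.
- Card sort, block design, digit span and following instructions: baseline EYT expressive vocabulary, EYT Go/No-Go, or both.

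The trial statistician may prefer other pairings; what matters is that they are named in advance and kept few. Age and sex stay in the model.

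The cost is one sentence here and in the analysis plan, and one or two child-level covariates per model. No new data are needed, and the sample size calculation does not change.

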#### Mediator analyses

Mediator analyses will aim to identify active components of the intervention and elucidate the pathways to change. To this end, the following three questions will be examined: whether improvements in maternal sensitivity and reciprocity and cognitive scaffolding mediate improvements in child cognition; whether increases in maternal sensitivity, reciprocity and mental state talk mediate improvements in child social understanding; and whether increases in maternal sensitivity, reciprocity and mental state talk and improved behaviour management strategies mediate improvements in child behaviour, and emotional regulation.

#### Moderator analyses

Moderator analyses will be conducted to investigate whether certain groups respond differently to the intervention. In addition to the potential moderators listed above, we will examine the impact of number of intervention sessions attended. Potential mediators and moderators of the intervention will be examined using mixed linear models or structured equation modelling, as appropriate.

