#### Hypotheses

##### Primary hypothesis

Compared to control group children whose carers receive no additional intervention, children whose carers receive the programme will show evidence of significantly better cognitive outcomes (i.e., observed language, sustained attention and executive function, and parent report).

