Weekly supervision was provided to the facilitators throughout the intervention phase of the study. LM and PJC met with the facilitators for an hour each week to review how the sessions went over the previous week. The two facilitators discussed aspects that went well, challenges, and logistical issues. They also identified any participants who were experiencing difficulties in applying the programme with their child, and discussed the support they may need in their next session. Finally, the group reviewed the attendance records from the past week and discussed plans for catch up sessions with any participant who may have missed sessions. The number of sessions each participant attended was recorded.

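### Number of sessions attended is classed as a moderator, but it arises after randomisation and only in the index arm, so what can be estimated is a self-selected dose comparison and not effect modification

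*Protocol article*

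**What the plan says.** The Moderator analyses section of the protocol article gives its purpose: "Moderator analyses will be conducted to investigate whether certain groups respond differently to the intervention". The next sentence adds attendance to the set: "In addition to the potential moderators listed above, we will examine the impact of number of intervention sessions attended". The section then names one model family for everything in it: "Potential mediators and moderators of the intervention will be examined using mixed linear models or structured equation modelling, as appropriate".

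The earlier list, under Potential moderators, begins: "The following variables will be used as potential moderators: family socio-economic status, parental education, monolingualism status, ethnic group, parental mental health". It continues with stress, baseline book-sharing, and the child's sex, age and birth order. All of these can be defined in both arms at baseline. Attendance is not on that list.

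Three other places fix what attendance is in this trial:

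- The intervention, facilitators, training and supervision: "The number of sessions each participant attended was recorded". The same paragraph says that catch-up sessions were planned for carers who missed any.
- Study design: the index Centres receive the training, "and a control condition (6 Centres) receiving the normal input from the Children’s Centres".
- Primary hypothesis: "Compared to control group children whose carers receive no additional intervention".

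The Data analysis section uses intention-to-treat for intervention effects and adjusts for the child's age, sex and, where there is one, the baseline score.

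**The concern.** A moderator analysis asks whether the randomised effect differs between groups that existed before allocation, each containing index and control members. Attendance does not define such groups. It follows from allocation, it is shaped by the carer's circumstances and the facilitators' catch-up efforts, and it has no counterpart among controls. Nobody can say which control carers would have attended seven sessions and which two.

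An analysis of attendance as a moderator therefore falls back on comparing index carers with one another. Carers who attend more may differ in motivation, stress or home circumstances, and these may relate to the child's language or attention whatever the programme does. The risk is that such differences are reported as a gradient in the programme's effect, under a heading that implies a randomised comparison.

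**Working it through.** **1. The sample size used as input.** The article gives no figure for attendance. The check uses its 96 carers per arm. That figure reproduces with 6 Centres per arm, 96/6 = 16 carers per Centre and the stated intra-cluster correlation of 0.04: design effect 1 + 15 × 0.04 = 1.60. At d = 0.66, two-sided alpha 0.05 and 12 − 2 = 10 degrees of freedom, power is 0.902. With 10% loss, 96/0.9 = 106.7, so 107 per arm and 214 in total, as stated.

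**2. Can the interaction be estimated?** The moderator model is

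outcome = b0 + b1·arm + b2·sessions + b3·(arm × sessions) + error.

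Controls have arm = 0 and sessions = 0. Index carers have arm = 1, so arm × sessions = sessions. The last two columns are identical for everyone. A numerical check with 96 per arm gives rank 3 for 4 coefficients. Only b2 + b3 can be estimated, and it is the slope on sessions within the index arm.

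**3. How far can that slope mislead?** Assumptions, none from the article: attendance centred on 5 sessions with SD 1.5, rounded and limited to 0–7; an unmeasured family factor correlated 0.5 with latent attendance and r with the outcome; outcome SD 1; no effect of sessions; no clustering; no covariates. The expected slope is roughly 0.5 × r / 1.5; for r = 0.3 this is 0.15/1.5 = 0.10 SD per session. Simulation with 96 index carers, 2,000 trials per row:

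| r (factor with outcome) | Mean slope, SD per session | Trials with p < 0.05 |
|---|---|---|
| 0 | 0.00 | 5% |
| 0.2 | 0.07 | 15% |
| 0.3 | 0.10 | 28% |
| 0.4 | 0.14 | 48% |

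Adding a constant programme effect of 0.66 SD, the same at every level of attendance, changes these results little. For scale, the planned effect spread evenly over an assumed mean of 5 sessions is 0.66/5 = 0.13 SD per session. A spurious slope of 0.10 to 0.14 is of that same order.

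**4. What does baseline adjustment do?** In a second assumed scenario the factor correlates 0.3 with attendance (SD 1.2) and 0.5 with both the baseline and the later score. The unadjusted slope is about 0.3 × 0.5 / 1.2 = 0.125 by formula and 0.12 in simulation, significant in 28–30% of trials. With adjustment for the baseline score:

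| Baseline–outcome correlation (assumed) | Mean slope | Trials with p < 0.05 |
|---|---|---|
| 0.5 | 0.06 | 12% |
| 0.6 | 0.05 | 11% |
| 0.7 | 0.04 | 9% |

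Adjustment reduces the bias and does not remove it. Table 2 schedules no baseline for CELF-2, EYT card sort, WPPSI block design, digit span or following instructions, all within the primary outcome domain. For these, adjustment for the child's own starting score is not possible.

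**5. What would allocation-based estimation give?** With zero sessions in controls and allocation as the only instrument, the per-session effect is essentially (index mean − control mean) / (mean sessions in the index arm). This rescales the intention-to-treat effect. It assumes a linear dose and that allocation acts only through sessions attended. Inference must also allow for 12 Centres. With no effect, an intra-cluster correlation of 0.04 and 16 carers per Centre, uncorrected cluster-robust standard errors with normal critical values reject in about 10% of trials. A standard correction with 11 degrees of freedom brings this to about 6–7%.

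**The case against.** The strongest reply is that the article commits to very little here. It says only that the impact of attendance will be examined. It writes down no arm-by-sessions interaction, and no stated hypothesis concerns attendance. The models are left open: "will be examined using mixed linear models or structured equation modelling, as appropriate". The sentence could be an ordinary exploratory look at dose in the index arm, with details left to an analysis plan that is not shown. This stands in part: a reader might infer that the authors will fit the inestimable interaction, and the text does not say so. It does not remove the point. The sentence joins attendance to the moderators, under that heading and for the stated purpose of finding groups that respond differently, and nothing marks the comparison as non-randomised. That is a classification the article makes, not a detail it omits.

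Three stronger readings are tempting and lack support:

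- That the trial's main result is compromised. Intervention effects are analysed by intention-to-treat, and no hypothesis or sample size depends on attendance.
- That the dose result will decide how many sessions are commissioned. The dissemination section promises recommendations for policy and practice but does not mention session number, and the programme is a fixed seven-session curriculum.
- That this trial's false-positive rate would be some particular figure, such as 28%. Every rate above rests on assumed correlations, and the unadjusted rates omit the baseline adjustment that the article specifies where a baseline exists.

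It is also fair to object that an instrumental-variable estimate is no complete answer. It cannot show whether attending more sessions matters. Its exclusion restriction is doubtful too: families keep the weekly books and are sent two more during follow-up, so allocation may act partly outside the session count.

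**Conclusion.** The point holds as a fault of classification. From the article's own description, sessions attended is post-randomisation and exists only in the index arm, so effect modification by attendance is not identified. This needs no numerical assumption. The index-arm slope that remains is open to self-selection. The size of that bias is not known from the article: over the assumed range, the unadjusted false-positive rate for a null dose effect runs from about 5% (no confounding) to about 48%. It is lower after baseline adjustment, where a baseline exists.

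The analysis is secondary and exploratory, and the primary intention-to-treat analysis is unaffected. It should be corrected before analysis; it is not a must-fix.

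**What to change.** Remove sessions attended from the moderator analyses and restrict moderators to variables measured at baseline. Since Table 2 schedules HADS and PSI at all three assessments, say that their baseline values are the ones used.

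If attendance is examined, report it as supplementary to intention-to-treat, in one or both of these ways:

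- **Allocation-based per-session effect.** Instrumental-variable estimation with Centre allocation as the instrument and sessions set to 0 in controls, using the covariates of the main model. State linearity and the exclusion restriction as assumptions, with the books kept by and posted to families named as a possible breach. Use small-sample-corrected inference suited to 12 Centres.
- **Index-arm dose description.** Regress outcome on sessions within the index arm, adjusted for baseline predictors of attendance, and label the result explicitly as a non-randomised comparison.

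The cost is a change of wording and one or two supplementary models on data already recorded. The downside is a wider interval and a weaker claim about dose. No sample size or primary analysis changes.
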